Accordingly, more actors are needed to offer support, not least non-government organizations. Value-based organizations have the advantage that they have more detailed knowledge of the problems. Junis is an NGO that works with children in Sweden. In addition to working with alcohol and other drugs issues, Junis is concerned with solidarity and democracy issues. Over the country, there are more than 12,000 members aged 6–15 years divided into about 175 local chapters. The organization is run by approximately 1300 voluntary trained leaders. In addition to Junis’s continuous weekly activities, every year throughout the country, a large number of camps are organized, as too are extensive activities in connection with the Christmas and New Year celebrations. Advocacy and education work supporting the needs of children who grow up in a family with harmful use of alcohol and drugs have been important part of Junis’s work plan for more than a decade.

In order to meet these challenges, the present research has been developed using three different complementary approaches: a universal approach through implementation of the curriculum in school classes, a selective approach through groups in the local chapters of Junis, and an indicative approach though groups recruited through the social services as support for the children of alcoholics.

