The method is theoretically promising and builds on principles of successful preventive and promotional work, but it has never been tested or researched in Sweden. We believe it can be an important element in the support offered to children, and their relatives and teacher/group leaders. However, it should be stressed that it is not a way of replacing actions at the structural level carried out by municipalities or county councils; successful promotive and preventive work needs to be implemented on many levels and by many different actors. RESCUR is a method to complement other efforts made by society in to provide children and relatives with improved protective tools so that they, in case of difficult situations, can not only handle the situation but also be strengthened. In other words, it is about helping children to get as good life chances as they possibly can.

The RESCUR program has a training component for the teachers and group leaders who will implement the curriculum. The training lasts 3 days. First, there is a two-day introduction to the theory and methodology of RESCUR, which also includes practical exercises. The teachers and group leaders are supervised through a monitoring visit to the different sites every sixth month for RESCUR in Sweden. The supervisors also observe the implementation and document results on an implementation checklist. There is also a one-day educational session for follow-up.

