### Research design and methodology

The project has been divided into three phases. The first phase involved planning and conducting a preliminary study, including the application to the research ethics committee (first year). We started the project, formed a project team and appointed a project manager, worked on the manuals to make them more user-friendly, gave information about and marketed the project among organizations and policy-makers, recruited participants for the evaluation, finalized the project and research plan, including all measuring instruments. The Ethical Review Board approved the research project (EPN dnr 2016/460).

The project is based on close collaboration between Junis and the research group, with a clear division of work and responsibility. The purpose of Junis’s activities is to provide health promotion for children aged 7–15 years in an encouraging environment where the child’s self-esteem and self-confidence grow together with secure and safe adults. The organization will be responsible for planning and implementing the program in all groups. The research group is responsible for the scientific study of implementation and effects of the program for the participants in groups and school classes who are part of the intervention and control groups. The research consists in a randomized, controlled, longitudinal survey of the RESCUR program. This means taking baseline measurements before the intervention begins, and follow-ups at 6 months, 1 year, and then 2 years.

The second phase involves implementing the program “I want, I can, I dare” (RESCUR) in Junis’s group activities, in groups throughout social services and in school classes in different municipalities and across the country (i.e., in different residential areas). The third phase involves analysis and reporting on the project’s implementation and its effects.

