**Table 1 Tab1:**
[figure not shown]
Schedule of enrolment, interventions, and assessments

The controlled study has three different arms. In the case of schools, we cluster-randomized participants to one of two conditions: (A) intervention schools or (B) waiting list or control schools. Randomization has been done at school level. Thereafter, the baseline measurements were performed in both conditions, and, after that, the intervention group began its activities, and measurements were taken as described above (Table 1). One year after the baseline measurement intervention group (A), the waiting list group began its program. Measurements are finally to be made a year later.

In the case of Junis’s groups, it was not feasible to do a cluster randomization at the managerial level as the involvement of local chapters was more difficult to achieve. The groups will be led by regular Junis volunteers.

As for the social services group, we will have the same arrangement, but no waiting-list control condition. Here, a new round of groups is planned for the second year. On the other hand, we will have a follow-up measurement of the first wave’s intervention groups in year 3 for both the Junis and the social services groups. The groups will be run by social workers.

However, it will be possible to compare developments in these two study arms with the data collected in the control schools.

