Recruitment for the evaluation of RESCUR in the social services groups is ongoing. At present, several social-services units have expressed an interest in being included in the evaluation. We will recruit participants to 8 groups with approximately eight participants for the first year. Here, there will be no randomization, but a second round of groups is scheduled for the second year. It provides a total of 128 children over the 2 years. The planned size of the sample in social services is less, since previous research has clearly shown that interventions in targeted or selected groups have a significantly higher effect size than those in universal groups (i.e., the school). The age of participants in the social services groups will be 7–9 and 9–12 years. During 2017, RESCUR groups have started in social services in five municipalities, including 42 children. Fifteen group leaders from six municipalities have received the RESCUR training so far.

For groups within Junis, 22 leaders from ten different districts have been asked to participate. We plan to have a total of 16 groups of approximately 8 participants in the Junis group. It provides 128 participants. The age of the participants will be between 7 and 12 years. Eight Junis leaders from 5 municipalities have been trained, but so far only one group has started to use the RESCUR intervention.

An important question to answer in the project is how the recruitment of participating actors as well as children is facilitated in the three types of organization. Another important question is whether the RESCUR method works equally well for children in the three types of organizations.

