### Data management and analysis

All collected material from surveys, observations and interviews will be encoded before analysis. The code key, with the researcher’s name and code number, will be stored separately in fireproof locked cabinets, which only research director [name] has access to. All collected material will be stored for at least 10 years in other fireproof archives, as required by law. All primary data will be stored at Göteborg University. Because the project has a longitudinal design, the research participants are not anonymous. However, it is of the utmost importance that the principle of confidentiality is followed. The names, addresses or the like of the children, parents or co-workers will not be read-in without being treated confidentially and only for this project. The results are only reported at group level, which means that individuals cannot be identified.

The research group has monthly meetings together with the implementing organization in order to facilitate the smooth running of the intervention study. In order to answer the five research questions, both quantitative and qualitative analyses will be applied in this intervention study, which uses a mixed methods research approach. The quantitative data will be managed using SPSS as a tool for analysis. In the randomized trial, we will use latent change models to examine the changes in child outcomes over time. To obtain unbiased estimates despite attrition, we will employ intention-to-treat analysis. Cohen’s *d* effect sizes were computed to estimate the effects of the programs compared with the wait-list condition while taking the initial level of each outcome measure into account. The social services and the NGO groups will be compared with controls matched from the waiting list controls. Mediating and moderating factors will be analyzed with regard to the primary outcomes.

The interviews will be transcribed and analyzed by qualitative content analysis. All sources of data will be used in the implementation study, where the inferences will be drawn using mixed-methods procedures.

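### Compared only with school controls, the Junis arm cannot separate RESCUR from Junis's own weekly activity, so question 5 mixes prevention level with setting

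*Protocol article*

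**What the plan says.** Three settings are studied, and only the schools are randomised. For the NGO, the Design section (text after Table 1) says "In the case of Junis’s groups, it was not feasible to do a cluster randomization at the managerial level". For social services it says "we will have the same arrangement, but no waiting-list control condition". The comparator for both is given twice. The Design section says "it will be possible to compare developments in these two study arms with the data collected in the control schools", and Data management and analysis makes this a plan: "The social services and the NGO groups will be compared with controls matched from the waiting list controls".

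The article also describes what Junis does apart from RESCUR. Research design and methodology gives the purpose of its activities as "health promotion for children aged 7–15 years in an encouraging environment where the child’s self-esteem and self-confidence grow together with secure and safe adults". The Background (Children's vulnerability) adds: "In addition to Junis’s continuous weekly activities, every year throughout the country, a large number of camps are organized". RESCUR is to be implemented within Junis's group activities, led by the organisation's usual volunteers. Social-services groups are recruited to support children of alcoholics and are run by social workers.

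Effect sizes are to take the starting value of each outcome into account. In the Discussion, question 5 (whether the intervention works differently at the universal, selective and indicated levels) is answered by comparing effect sizes across the voluntary organisation, social services and school, supplemented by leader interviews and observations.

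**The concern.** In the randomised school comparison both sides attend ordinary school and only one receives RESCUR, so the contrast isolates RESCUR. In the Junis comparison the treated children also take part in an organisation whose stated purpose overlaps with the intervention. Building self-esteem is Junis's aim and is also part of theme 5, one of the three RESCUR themes being evaluated. The control condition does not provide this.

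This is a different problem from whether the children are alike. Perfect matching on age, sex, family situation and baseline score would still leave two exposures delivered together on the treated side.

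The consequence falls mainly on question 5. Participants and recruitment already expects targeted groups to show larger effects than universal ones. A larger Junis estimate would look like confirmation of that, although the setting could have produced it.

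**Working it through.** **Inputs (all from the protocol article)**
- Selective groups: d = 0.5, power 0.8, two-sided alpha 0.05, 64 per group (Participants and recruitment).
- Universal arm: d = 0.3, power 0.8, 176 per group (same section; alpha is not stated for this figure and is taken as 0.05 two-sided).
- Planned children: social services 8 groups × 8 × 2 years = 128; Junis 16 groups × 8 = 128.
- The article gives no effect for Junis's or social services' own activity. Any value used below is an assumption.

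**Step 1. The plan's own figures.** Per-group n = 2(z₀.₉₇₅ + z₀.₈₀)²/d² = 15.70/d².
- d = 0.5: 15.70/0.25 = 62.8, so 63. The t-test version gives 63.77, so 64, as stated.
- d = 0.3: 15.70/0.09 = 174.4, so 175. The t-test version gives 175.4, so 176, as stated.

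Both reproduce with individual-level formulas. No stated number is in dispute.

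**Step 2. What each contrast contains.** Let r be the effect of RESCUR in a setting and b the change that the host organisation's other activity adds between baseline and follow-up.

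| Arm | Treated side | Comparator | Contrast, apart from selection |
|---|---|---|---|
| School (randomised) | RESCUR in school | ordinary school | r |
| Junis | RESCUR within Junis activity | matched school controls | r + b |
| Social services | RESCUR in a social-services group | matched school controls | r + b, where b may be zero |

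For Junis, the article itself describes an activity that could make b non-zero. For social services, it describes none separate from the RESCUR group.

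**Step 3. What adjustment does.** Suppose the club has already contributed B₀ before baseline. Adjusting for the starting value accounts for B₀ and leaves b, which accrues afterwards. Matching on child characteristics affects selection, not b.

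**Step 4. Illustration of size.** Set r = 0 and assume no other bias. The chance of a significant two-sided result at 0.05 is the two-sample t-test power at d = b, with noncentrality b√(n/2). For example, b = 0.3 and n = 64 gives 0.3 × √32 = 1.70.

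| b (assumed) | 64 per group | 128 per group | RESCUR effect if the observed d is 0.5 |
|---|---|---|---|
| 0.1 | 0.087 | 0.125 | 0.4 |
| 0.2 | 0.202 | 0.357 | 0.3 |
| 0.3 | 0.391 | 0.667 | 0.2 |
| 0.5 | 0.801 | 0.979 | 0 |

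These ignore clustering and any precision gained from baseline adjustment. They show sensitivity and do not estimate the bias.

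**Step 5. Effect on question 5.** The cross-arm difference is (r_Junis + b) − r_school. If RESCUR worked equally in both settings with d = 0.3, then b = 0.5 − 0.3 = 0.2 would by itself produce the gap between the two effect sizes assumed at planning.

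**The case against.** Several points on the other side stand.

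- **Social services.** A reader might infer that these children also receive RESCUR on top of other support. The article does not say so. It speaks of RESCUR groups having started in social services, so the RESCUR group may itself be the support. The remark that "RESCUR is a method to complement other efforts made by society" does not help, because it is a general statement about the method and applies equally to the schools.
- **All treated and no controls exposed.** A reader might infer this from the design. Waiting-list status withholds only RESCUR. Nothing prevents a control child from attending Junis, another club or a support group. What can be said is that the control condition does not supply such activity.
- **Credit wrongly given to RESCUR.** A reader might infer that the comparison overstates the effect. The direction is not established. RESCUR may displace part of the usual Junis session, established members' earlier gains are in the baseline, and the higher risk of social-services children could bias their contrast the other way.
- **Disclosure.** The article says openly that these arms lack randomisation or an own-setting control, ties its latent change models to the randomised trial, and adds qualitative material to question 5.
- **No listed item on other support.** An article condenses its questionnaire, so this absence is not held against the plan.

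None of this resolves the Junis contrast. The comparator is stated, the concurrent activity is described, and the effect sizes are to be set beside the randomised school result. Disclosing the lack of randomisation does not tell a reader that the exposures differ by more than RESCUR.

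**Conclusion.** The point holds for Junis and is possible, but not shown, for social services. Without a same-setting control, the Junis estimate combines RESCUR with what Junis's ordinary activity adds during follow-up, and the question 5 comparison mixes prevention level with setting. Up to 128 planned Junis children are affected, possibly also the 128 planned in social services, and chiefly one of the five research questions. The randomised school comparison is untouched.

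The size and net direction of the bias are unknown. The probabilities in the illustration rest on assumed background effects, a null RESCUR effect and no opposing bias. The conclusion itself needs only two things from the article: that RESCUR runs inside Junis activity with overlapping aims, and that the comparator is ordinary school.

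**What to change.** In Data management and analysis, and in the Discussion of question 5:

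1. Define the Junis contrast as *RESCUR delivered within Junis activity versus ordinary school*, and the social-services contrast as *RESCUR delivered in a social-services group versus ordinary school*. State that both are non-randomised.
2. Base claims about the effect of RESCUR itself on the randomised school comparison.
3. Report effect sizes by arm if wanted, but do not attribute differences between arms to RESCUR or to prevention level.
4. Optionally, ask one item on club membership and other support in all arms, including the school controls. It would describe exposure. It could not separate the components if nearly all treated children share the background activity.

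The cost is revised wording, at most one questionnaire item, and a narrower claim under question 5.

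A lead-in period may look attractive, since at the time of writing "so far only one group has started to use the RESCUR intervention" in Junis, which leaves 15 of the 16 planned groups. Measuring change under ordinary Junis activity for a semester before RESCUR is not recommended as the main comparison. It would replace a concurrent control with an uncontrolled before-and-after contrast open to maturation, season and repeat testing. It also assumes that the groups already meet, and it delays delivery in a 2017–2019 study with two-year follow-up.

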But we also know that far from all children can get access to the support available in society. Estimates have shown that between 4 and 5% of all Swedish children under the age of 18 live with a parent who has harmful use of alcohol/drugs [40, 41]. Studies at the Center for Health Equity Studies (CHESS) followed children born 1987–89 (*N* = 332,000) up to adulthood, and parents who were abusing or had addiction problems were identified via different registries. A total of 4% of all children had at least one parent who had been treated for harmful use of alcohol (2.5%) and drugs (1.5%) at childbirth [41]. In-depth analysis of the survey from 2012 showed that 56% of these parents want to talk about their parenting, but only 24% of the children living in families where a person was being treated for a dependency disorder was given formal support [42]. A minority of children receiving support already had problems of their own.

Another source of information on support for children in families where at least one parent has harmful use of alcohol/drugs is the report published annually by Junis (IOGT-NTO’s Junior Federation), now in its 12th consecutive year. It is based on surveys of Swedish municipalities, of which 73% participated in 2015 [43]. In 2005, 57% of municipalities had special support groups for children with a parent with harmful use. The proportion was 66% in the report published in 2015. However, in this report, the answers refer not only to support groups but also to individual support. And the number of participants in the various municipalities varied greatly. Conclusions from the different surveys are that there were major regional differences, and that there is a great need for increased efforts to strengthen the child and parent perspective in various parts of social services. Moreover, there is a great need for support for these children as only a small proportion receive formal support.

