## Methods/design

### Aims

The primary aims are to strengthen protective factors and promote childhood life changes for 7–14 year-olds who are relatives of people with addiction problems, and to contribute to the support that Swedish society gives to these children. We want to break the pattern of alcohol and drug problems being transmitted between generations. This entails a preventive intervention targeted at those who have an increased risk of developing addiction problems and other problems that are consequences of their situation. A secondary aim at the universal level is to promote protective factors among children of the same ages, and to prevent the development of drug addiction among children.

In order to increase our chances of achieving these goals, we are implementing the project as a collaboration between practitioners and researchers. Our goals also include increasing the relevance of the project, developing knowledge, and improving practical implementation. This can also provide an increased opportunity to disseminate experiences to other groups, and for other activities, after the method has been tested and evaluated based in the Swedish context and in three priority areas – social services, a NGO, and schools.

The research covers five research questions:How can participants in the implementation of the program be recruited?How can leaders be supported to enable the implementation of a high-quality program?What is the significance of the program for children’s development and mental health?Does the program work differently for different groups in relation to gender, social background, place of residence and age?Does the intervention work differently at a universal, selective or indicative level?

The research questions will be studied through an implementation evaluation, using self-assessment forms, interviews and observations using an established “checklist”, as well as through an impact assessment, which has a randomized, controlled pre-post design, in which self-reports, interviews and adult reports of testing instruments are used. Our main target group consists of children aged 7 to 12 years who are in one of the organization’s schools, social services or the value-based organization IOGT-NTO Junior Federation, Junis. A secondary target group consists of the deliverers.

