#### Self-reports from the children

All measures have been translated into Swedish in previous research projects, and the psychometric tests have been shown to work well in the age groups we are evaluating. The instruments that we will use are the following:Child and Youth Resilience Measure (CYRM) [52]. In order to make the evaluation as change-sensitive as possible, we will use the variant with a 5-point Likert scale, instead of the 3-point.How I feel (HIF) [53] is used for older children, and further development of the instrument for younger ages is underway in our EU Comenius Project European Assessment Protocol for Children’s SEL skills [How one feels (HOF)].Health, psychiatric symptoms, somatic symptoms and health behaviors from HBSC (Health Behaviour of School-aged Children) [54, 55],Mastery [56]Demography (gender, age, housing situation, family structure).

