#### Reports from adults

At least one adult per child will fill in instruments about the child’s behavior. For the school group, this will be the child’s teacher. For the social services group, it is primarily a parent, or secondarily a social worker, who will respond. For the Junis groups, leaders are assessing the behavior of the child. The adults will fill in two instruments. Both instruments have previously been translated into Swedish, and both have been shown to have good psychometric properties.Child and Youth Resilience Measure - Person Most Knowledgeable (CYRM) [33, 57]. In order to make the evaluation as change-sensitive as possible, we will use the variant with a 5-point Likert scale, instead of the 3-point. This is exactly the same measure that the children themselves may fill in.Strengths and difficulties questionnaire (SDQ) [58, 59]. SDQ is an international and widely used instrument, and is also a widely used measure in Sweden.

The school classes and groups who will fill in surveys will receive as small economic token in appropriate forms from the research project.

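### Effects in the primary-aim population rest on non-randomised contrasts with general-school controls, which the plan should label observational and limit to child self-reports up to 1 year

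*Protocol article*

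**What the plan says.** The Aims section of the protocol article places "7–14 year-olds who are relatives of people with addiction problems" in the primary aims. It then adds: "A secondary aim at the universal level is to promote protective factors among children of the same ages". The same section announces "an impact assessment, which has a randomized, controlled pre-post design".

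The Design section limits the randomisation to schools: "Randomization has been done at school level". It reports that cluster randomisation was not feasible for the Junis groups and that the social services arm has no waiting-list control. Participants and recruitment confirms that social services will not be randomised. The Design section nevertheless notes that both arms can be compared with the control schools, and Data management and analysis makes this the plan: "The social services and the NGO groups will be compared with controls matched from the waiting list controls".

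The Discussion answers research question 5 (universal, selective or indicated level) by comparing effect sizes between the three arms, from child and adult reports.

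Four further statements bear on the comparison:

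- Prevalence (Children's vulnerability): "between 4 and 5% of all Swedish children under the age of 18 live with a parent who has harmful use of alcohol/drugs".
- Background variables (Self-reports from the children): "Demography (gender, age, housing situation, family structure". Parental substance use is not listed.
- Adult informant (Reports from adults): "For the social services group, it is primarily a parent, or secondarily a social worker, who will respond". In schools it is the teacher, and in Junis the group leader.
- Timing (Design): the waiting-list schools begin the programme 1 year after baseline, while follow-up runs to 2 years. Adult reports are taken only at baseline and 1 year.

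**The concern.** Randomised evidence is available for children in general. The children named in the primary aim are reached mainly through arms that were not randomised, and their comparator comes from ordinary school classes. The article says openly that these arms are not randomised. It does not say what follows for interpretation: nowhere is the matched contrast called observational, and it is powered as a two-sided test of group differences.

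Three separate problems arise:

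1. In the social services arm, the feature that brings a child into the arm is probably rare among the controls and is not listed as measured in them.
2. In both arms, the adult-reported CYRM and SDQ come from a different kind of rater than in the controls.
3. At 2 years the controls are no longer untreated.

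A programme effect could therefore be claimed or dismissed for vulnerable children on a difference that reflects who they are or who rated them. Research question 5 would also set a randomised effect size beside two confounded ones as if all three were of the same kind.

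**Working it through.** **1. The three arms side by side**

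| Arm | Allocation | Comparator | Adult informant |
|---|---|---|---|
| School | Randomised by school | Waiting-list schools | Teacher, in both conditions |
| Social services | Not randomised | Matched school waiting-list children | Parent, otherwise social worker |
| Junis | Not randomised | Matched school waiting-list children | Group leader |

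Only in the first row are allocation and type of informant the same on both sides of the comparison.

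**2. The plan's own figure.** Inputs from Participants and recruitment: d = 0.5, power 0.8, two-sided alpha 0.05.

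n per group = 2 × (1.960 + 0.842)² / 0.5² = 62.8, so 63 by the normal approximation. The two-sample t-test gives 63.8, so 64. The stated 64 reproduces; the problem is not arithmetic.

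**3. Controls expected to share the exposure (social services only).** Inputs: 401 waiting-list children (Participants and recruitment) and 4 to 5% (Children's vulnerability).

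- 401 × 0.04 = 16.0
- 401 × 0.05 = 20.1
- At an assumed 10% in these schools: 401 × 0.10 = 40.1

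The 4 to 5% is a national figure applied to nine schools, so this is an inference. Even at the assumed 10%, the count stays below the 64 per group on which the contrast is powered.

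**4. What a like-for-like comparison could detect.** Suppose the exposed controls could be identified and were the only ones used. Power at d = 0.5 is about Φ(0.5 / √(1/n₁ + 1/n₂) − 1.96). With 16 per group this is Φ(1.414 − 1.96) = 29%, and with 20 per group Φ(1.581 − 1.96) = 35%. The t-test gives slightly less:

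| Intervention children | 16 exposed controls | 20 exposed controls |
|---|---|---|
| Matched 1:1 | 28% | 34% |
| 64 | 42% | 49% |
| 128 | 47% | 54% |

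An exposure-matched contrast at the planned power is therefore not available from this pool. Any matched set of about 64 or more must consist largely of children without the exposure, and must rely on other measured variables to stand in for it.

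**5. What leftover confounding would do.** The documents give no size for it, so this is an illustration. With no programme effect and a residual group difference of b SD, the rejection rate is 1 − Φ(1.96 − δ) + Φ(−1.96 − δ), where δ = b / √(2/n).

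| Assumed b | n = 64 per group | n = 128 per group |
|---|---|---|
| 0.1 | 9% | 13% |
| 0.2 | 20% | 36% |
| 0.3 | 40% | 67% |

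Example: b = 0.2 and n = 64 give δ = 0.2 / 0.177 = 1.13 and a rejection rate of 20%, against a nominal 5%.

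**6. Timing.** Follow-ups are at one semester, 1 year and 2 years, and the controls start at 1 year. The usable untreated comparison therefore covers the first two follow-ups. Adult reports enter it only at 1 year, and there the informants differ.

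**The case against.** Several points on the other side have force.

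- **No matching variables are named.** An article may leave them to a fuller plan. A reader might infer that controls will be matched on baseline score and then put a size on regression to the mean. The documents support neither step: the remark about initial levels describes how Cohen's d is computed, and neither a pre-post correlation nor a population gap is given. On that reading, low-scoring controls would drift upwards and the programme's benefit would be understated, not created. No such bias figure is claimed here.
- **Exact matching on parental substance use is not strictly required.** The 64 is a power figure, not a required count of exposed controls. Symptom measures, Mastery and SDQ are also collected and could stand in for part of the difference. This stands, and it is why the conclusion is that the contrast cannot be relied on, not that it must be biased.
- **Junis is not an arm of children with addicted parents.** The Background section calls it selective and states no such entry condition. A reader might carry the 4 to 5% argument over to Junis; the documents do not support that.
- **The primary aims read as programme goals.** Research questions 3 and 4 concern children generally, and the school trial addresses them. This is fair, but the primary-aim population and research question 5 still depend on the non-randomised arms.
- **Informant differences may partly cancel.** If the same adult reports both times, a stable difference drops out of a change score. Differing sensitivity to change does not, and in Junis the rater also leads the group.
- **The lack of randomisation is disclosed.** That is so, and the phrase about unbiased estimates concerns attrition in the randomised trial. Disclosing the allocation still leaves open what may be concluded from the contrast.

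A fuller plan could name matching variables. It could not supply randomisation, untreated controls at 2 years or, on the article's figures, enough exposed controls.

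**Conclusion.** The point holds in this form. The randomised evidence serves the universal aim. For the social services arm, about 16 to 20 of 401 controls are expected to share the defining exposure, which is not among the child variables listed, so the matched contrast cannot be relied on for an unbiased effect. For Junis, the weakness is non-randomised allocation and a different adult informant. For both arms, adult-report contrasts mix rater type with group, and 2-year contrasts have treated controls.

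The count rests on the national prevalence holding roughly in the nine control schools. The power and rejection-rate tables rest on the assumptions stated with them, and the size of any actual bias is unknown.

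A reader might conclude that the trial's effect evidence as a whole is compromised. It is not: the concern leaves the randomised school comparison untouched.

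**What to change.** In Data management and analysis, and in the Discussion's answer to research question 5:

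1. State that the randomised school comparison is the confirmatory effect analysis.
2. State that the social services and Junis contrasts with school controls are observational and exploratory.
3. Limit those contrasts to child self-reports at one semester and 1 year.
4. Do not use adult-report effect sizes compared across informant types as evidence for research question 5.
5. For each retained contrast, show both the change-score and the baseline-adjusted estimate as a sensitivity analysis. They rest on different assumptions about how the groups would have developed, so disagreement is informative; agreement does not prove absence of bias.

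The cost is some rewording and one additional analysis per retained contrast. The downside is weaker claims for the targeted arms and no controlled 2-year or adult-report result for them. These steps do not remove confounding by parental substance use; they keep the conclusions within what the design can support.
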